### Quality control

To maintain the quality of the study, the directors at each center will form a steering committee that will review study progress, resolve any problems, and guide the process of implementation. All investigators from each center will receive training to unify study criteria and procedures across centers. Two investigators will collect study data simultaneously. To reduce subjective bias, two clinical investigators will evaluate the diarrhea data independently during the follow-up period. Two chief oncologists will evaluate chemotherapy response, and if necessary they will modify the predetermined chemotherapy regimens. Any discrepancies in their evaluations will be adjudicated by a third chief oncologist.

The CRA in each hospital will manage the data and monitor trial progress according to the protocol by checking the informed consent and case report forms (CRFs) and the original results of the laboratory tests and imaging studies for each participant.

An independent third party (Beijing Qihuang Medicine Clinical Research Center, Beijing, China) will be responsible for monitoring and evaluating the data. They will also audit trial progress every 3 months and report any suggestions for optimizing the protocol and conduct of the study to the steering committee.

### Statistical analysis

The study data will be managed and analyzed by an independent biostatistician using SPSS (Statistic Package for Social Science, v20.0). This study includes four data sets for analysis: intention to treat (ITT), per-protocol set (PPS), full analysis set (FAS), and safety set (SS).

ITT analysis will be used to analyze the primary outcome for SXD efficacy in preventing or reducing the incidence and severity of CRD, and will include all study participants. Any missing primary outcome data will be supplemented by carrying forward the last recorded data.

PPS analysis will be performed to test the robustness of the ITT analysis and will only include participants who strictly follow the protocol and finish the study. The results from the two analyses will be considered credible if they are consistent; otherwise, the results will require sufficient discussion and explanation. Furthermore, is compliance is too low, CACE analysis will be implemented to provide an unbiased and robust estimation of treatment effect. The analysis of secondary outcomes will be based on the results of the PPS analysis.

The FAS analysis will include all randomized participants who completed at least one treatment and one follow up. To analyze the intervention-related AEs, the SS analysis will evaluate all safety outcomes for every randomized participant who received any intervention at least once during the study period.

Continuous data will be presented as the mean and standard deviation (SD), and noncontinuous data (including categorical or ranked data) will be presented as count and number (percentage). We will analyze categorical data as the risk ratio (RR) with 95% confidence intervals (CI), and analyze continuous data as mean differences (MD) and their 95% CI.

The incidence of diarrhea, modification rate of the chemotherapy regimen, and incidence of hospitalization are categorical data. The chi-square test or Fisher’s exact test will be conducted to compare the differences in those data between two groups. The Wilcoxon rank sum test will be conducted to evaluate the difference in ranked data between the two groups, which includes the grade of diarrhea and evaluation of chemotherapy efficacy. Repeated-measures analysis of variance (ANOVA) will be used to compare continuous values such as the use of antidiarrheal drugs. In all tests, a *P* value of < 0.05 will be considered statistically significant.

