**Methods and design:**

A prospective, double-blind, randomized, placebo-controlled trial will be conducted in patients with small cell lung cancer (SCLC) from five hospitals in China. For this study, 100 irinotecan-naïve patients will be randomly allocated to either the SXD or placebo arms in a 1:1 ratio. Stratified randomization will be used to divide subjects by UGT1A1 genotype into groups with differing risk of diarrhea. The trial will consist of two cycles of chemotherapy with 14 days of oral administration of SXD or placebo administered beginning between 3 days before and up to 11 days after initiation of each chemotherapy cycle. The primary study outcome is the incidence of diarrhea. Secondary outcomes include the degree of diarrhea, the degree of neutropenia, the rate of alterations in chemotherapy regimens, the amount of antidiarrheal drug taken, the rate of hospitalization, and evaluation of chemotherapy efficacy.

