### Outcome measurement

#### Primary outcome

The primary outcome measure is the incidence and percentage of CRD in each group. CRD is defined as diarrhea occurring > 24 h after irinotecan administration and up to the completion of both chemotherapy cycles.

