#### Secondary outcomes

Secondary outcomes include the degree of diarrhea, degree of neutropenia, incidence of chemotherapy regimen alterations, amount and dose of antidiarrheal drugs taken, incidence of hospitalization for diarrhea, and evaluation of chemotherapy efficacy.

Each participant will be supplied with a diary in which they will be instructed to record the time, duration, and coexisting symptoms of diarrhea. The information will then be reported to the researchers. The grade of diarrhea will be assessed for each chemotherapy cycle, and the most serious grade for each participant will be recorded to compare the difference in grades between the SXD and placebo cohorts. The diarrhea grading criteria used will be in compliance with the Common Terminology Criteria for Adverse Events (CTCAE), Version 5.0, released by the National Cancer Institute (NCI), which is detailed in Table 2. In addition, to completely evaluate each episode of diarrhea, participants will be instructed to record in detail the duration of diarrhea and the presence of coexisting symptoms, such as stomachache, abdominal distension, and cramps.

**Table 2 Tab2:** Diarrhea grading criteria

Grade of diarrhea	Definition
**Grade 1**	Increase of < 4 stools per day from baseline; mild increase in ostomy output compared to baseline
**Grade 2**	Increase of 4–6 stools per day from baseline; moderate increase in ostomy output compared to baseline; limiting instrumental ADL
**Grade 3**	Increase of ≥ 7 stools per day from baseline; hospitalization indicated; severe increase in ostomy output compared to baseline; limited self-care in ADL
**Grade 4**	Life-threatening consequences; urgent intervention indicated
**Grade 5**	Death

*ADL* activities of daily living

The development of diarrhea can affect the chemotherapy dose, duration, and schedule. Therefore, alterations in the chemotherapy schedule will be calculated in each group, including dose reductions, treatment postponement or termination, and other alterations in the preplanned chemotherapy regimen. If serious diarrhea occurs, antidiarrheal drugs and even hospitalization may be required, as determined by the recommended guidelines and expert consensus. The amounts and doses of antidiarrheal drugs prescribed and the incidence of hospitalization will be recorded. Common antidiarrheal drugs are loperamide and berberine hydrochloride [21, 22].

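### Diarrhea severity is placed inside the primary ITT analysis and is also a secondary outcome analysed per protocol; the two statements must be reconciled

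*Protocol article*

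**What the plan says.** All references are to the protocol article.

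- **Abstract, Methods and design:** "The primary study outcome is the incidence of diarrhea".
- **Primary outcome:** "The primary outcome measure is the incidence and percentage of CRD in each group". CRD is counted from more than 24 hours after irinotecan to the end of both cycles.
- **Sample size:** the calculation uses CRD incidence alone (37.5% with SXD, 63.4% without), two-sided 5%, 80% power.
- **Secondary outcomes:** "Secondary outcomes include the degree of diarrhea, degree of neutropenia, incidence of chemotherapy regimen alterations". Each participant's most serious grade is to be compared between arms.
- **Statistical analysis, primary analysis:** "ITT analysis will be used to analyze the primary outcome for SXD efficacy in preventing or reducing the incidence and severity of CRD". This analysis includes all participants, and missing primary-outcome data are carried forward from the last record.
- **Statistical analysis, secondary outcomes:** "The analysis of secondary outcomes will be based on the results of the PPS analysis". The PPS holds only participants who adhere strictly and finish.
- **Statistical analysis, tests:** for incidence, regimen modification and hospitalization, the chi-square test or Fisher's "exact test will be conducted to compare the differences in those data between two groups". The Wilcoxon rank sum test is for "ranked data between the two groups, which includes the grade of diarrhea and evaluation of chemotherapy efficacy". The threshold is general: "In all tests, a *P* value of < 0.05 will be considered statistically significant".
- **Subject withdrawal criteria:** participation ends on a severe adverse event during chemotherapy, on a chemotherapy schedule change forced by severe reactions, or on non-compliance.

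**The concern.** Severity cannot be both part of the primary ITT analysis and a secondary outcome on the PPS. Two things depend on which statement governs.

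1. **The analysis set for grade.** Under the primary-analysis sentence, the grade comparison includes everyone randomized. Under the secondary-outcome sentence, it includes only completers. A patient with severe diarrhea can meet a withdrawal criterion and so leave the PPS. The patients most informative about severity could thus be in one version of the comparison and out of the other.
2. **The status of a grade result.** With severity named in the primary-outcome sentence, a significant grade comparison beside a null incidence comparison could be presented as support for the primary claim. The trial's 5% error rate was set for incidence alone.

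**Working it through.** **Step 1. The role of severity, section by section**

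| Section | Role of severity | Analysis set |
|---|---|---|
| Abstract; Primary outcome; Sample size | not part of the primary outcome | – |
| Secondary outcomes | secondary | – |
| Statistical analysis, ITT sentence | within the primary-outcome analysis | ITT, last value carried forward |
| Statistical analysis, PPS sentence | (as a secondary outcome) | PPS |

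The third row conflicts with the first two on role and with the fourth on analysis set. No sentence makes grade an exception to the PPS rule.

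**Step 2. The plan's own figure**

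The Sample size section gives about 40 per group. The usual pooled two-sided formula is

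n = [1.960 √(2 p̄ q̄) + 0.842 √(p₁q₁ + p₂q₂)]² / (p₁ − p₂)²

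with p₁ = 0.375, p₂ = 0.634, p̄ = 0.5045:

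- 1.960 × √0.49996 = 1.386
- 0.842 × √(0.2344 + 0.2320) = 0.575
- n = (1.961)² / 0.0671 ≈ 57.3, so 58 per group.

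The stated 40 is not reproduced. Only the dropout step is: 40 / 0.80 = 50. This is a separate matter and the present point does not depend on it. What matters here is that the calculation uses incidence only and leaves no allowance for a second primary comparison.

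**Step 3. Error rate if a grade result were also accepted as primary success**

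This is conditional, because the protocol states no such rule. Inputs:

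- From the protocol: 50 per arm, 63.4% with any CRD (so 36.6% at grade 0), two-sided 5% for each test.
- Assumed: the split over grades 1–4, which the document does not give. Five splits were used, each summing to 63.4%: 30/20/10/3.4, 22/20/16/5.4, 35/18.4/8/2, 30/17/13/3.4 and 35/17.4/9/2 percent.
- Method: 40,000 simulated trials per split with identical arms; chi-square on any diarrhea, tie-corrected Wilcoxon on worst grade, everyone in both tests.

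Results:

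- For the 30/17/13/3.4 split, each test alone rejects in 5.0% (incidence) and 4.9% (grade), and at least one rejects in 7.2%. Both therefore reject in 5.0 + 4.9 − 7.2 ≈ 2.7%.
- Over the five splits, at least one rejects in 7.1% to 7.4%. The simulation standard error is √(0.072 × 0.928 / 40,000) ≈ 0.13 points, so the splits hardly differ.
- The two test statistics correlate at about 0.87.
- At other assumed incidences (50% and 80%, 50 per arm), the figure runs from about 6.6% to 8.6%.

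The excess at the protocol's incidence is thus about 2 percentage points.

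**Step 4. What the choice of set can remove**

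The Background gives 11–32% for grade 3–4 diarrhea with irinotecan. If that range applied and each such case led to withdrawal, 50 × 0.11 = 5.5 to 50 × 0.32 = 16 patients in an arm would leave the PPS grade comparison. Both conditions are assumptions. The range is from other studies, and the document does not say that every grade 3–4 case leads to withdrawal. The calculation shows only how many could be affected.

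**The case against.** The strongest reply is that this is loose wording. The ITT sentence speaks of one primary outcome, and the mention of severity can be read as a statement of the drug's purpose. Three sections name incidence, one expressly makes grade secondary, and the working hypothesis concerns the occurrence of diarrhea. This stands as the likely explanation.

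A reader might go further and infer that two tests at 5% can each decide the trial. The documents do not support that.

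- No section says that either result suffices, and a positive claim on grade alone would contradict the definition of the primary outcome.
- Tests are assigned by data type over all outcomes. Chi-square or Fisher also serves regimen modification and hospitalization, and Wilcoxon also serves chemotherapy efficacy, which is secondary. The separate test for grade is therefore no sign of a second primary test.
- The 5% threshold is a general convention for all tests.
- The figure for two independent tests, 1 − 0.95² = 9.75%, does not apply to two tests on the same diarrhea grades.
- A loss of power from requiring both tests to succeed has no basis in the text either.

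It can also be said that ordering among secondary outcomes belongs in an analysis plan that is not shown. That is right, and no such hierarchy is asked for.

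The reply does not remove the contradiction over the analysis set. Even if incidence alone is primary, the current text puts severity on ITT in one sentence and on PPS in another.

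**Conclusion.** The inconsistency is real, and it is modest in size. Severity appears both inside the primary ITT analysis and as a secondary PPS outcome. The sections taken together point to incidence as the sole primary outcome.

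The error rate of about 7% against 5% holds only if a significant grade result were accepted as primary success, which the protocol nowhere says. It also rests on assumed grade splits, 63.4% incidence and 50 per arm. It measures what the ambiguity could cost and does not describe the planned test.

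The analysis-set conflict needs no such assumption. It should be settled because the PPS can lose the patients withdrawn for severe reactions.

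**What to change.** In the Statistical analysis section:

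1. Limit the primary-outcome sentence to the incidence of CRD as defined under Primary outcome. State that the efficacy conclusion rests on that one comparison, SXD against placebo, on the ITT set at two-sided 5%.
2. State that worst diarrhea grade is a secondary outcome analysed on the ITT set, with PPS as sensitivity analysis, and amend the sentence on secondary outcomes to match.

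The second change is needed with the first. Striking severity from the primary sentence alone would leave grade on the PPS only, so patients withdrawn for severe reactions could drop out of the severity comparison. Testing grade formally only after a significant primary result is optional and can be left to the analysis plan.

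The cost is a few sentences, with no extra patients or data. The downside is that a grade-only benefit cannot be claimed as the primary result. The change should be made before unblinding, since a later choice between the two readings could look driven by the data.

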## Methods and designs

### Study design

The study will be conducted in five hospitals in Beijing, China, including China-Japan Friendship Hospital (Ethical Approval Document No. 2018–82-K57), Beijing Friendship Hospital Affiliated with Capital Medical University (2019-P2–016-02), Beijing Hospital of TCM Affiliated with Capital Medical University (2018BL-057-02), Wangjing Hospital of China Academy of Traditional Chinese Medicine (WJEC-KT-2018-045-P001), and Beijing Chaoyang Hospital Affiliated with Capital Medical University (2018-KE-313).

The study design flow chart is shown in Fig. 1. The trial will use stratified random grouping. Eligible subjects will first undergo UGT1A1 gene testing and be stratified to one of two levels, low or moderate-to-high risk of CRD, after which they will be randomly allocated to the SXD treatment cohort or the placebo cohort within their risk group. Patients will be excluded if UGT1A1 testing fails for any reason. The trial will include two cycles of chemotherapy (21 days per cycle), and each cycle will consist of 14 days of oral administration of SXD or placebo beginning 3 days before initiation of chemotherapy, with a follow-up visit from the initiation of chemotherapy. The trial schedule, including patient enrollment, interventions, and outcome measurements is shown in Fig. 2.

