### Sample size

The study proposes that SXD can reduce the occurrence of irinotecan-related diarrhea in patients with SCLC, which was the working hypothesis we used to calculate sample size. This study was designed as a superiority trial and sample size calculations are based on the primary outcome measurement - the incidence and percentage of CRD. Based on the results of our preliminary observational study and previous literature [18], the incidence of CRD is 37.5% (6/16) with SXD and 63.4% without SXD, respectively.

In our study, the ratio of subjects will be 1:1 in both the SXD and control groups. Sample size calculations were performed using PASS software, version 15.0, for a superiority test for two independent, randomized samples. With a significance level of 5% (α), a two-sided test, and power of 80% (1 − β), the required sample size was determined to be approximately 40 per group. Considering an estimated dropout rate of 20%, 50 subjects will be required per group, giving a total of 100 subjects.

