### Subject withdrawal criteria

Study participation will be terminated if:
A severe adverse event (AE) occurs during chemotherapy;The chemotherapy schedule requires modification because of severe adverse reactions to chemotherapy;Subjects do not comply with this study’s requirements.

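### Carrying the last record forward scores every patient who leaves before any diarrhea as free of CRD, which biases the comparison towards the arm that loses more patients while still event-free

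*Protocol article*

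**What the plan says.** The Primary outcome section states: "The primary outcome measure is the incidence and percentage of CRD in each group". CRD counts if it starts more than 24 hours after irinotecan and "up to the completion of both chemotherapy cycles". Study design sets the length of that window: "The trial will include two cycles of chemotherapy (21 days per cycle"), so 42 days in all. The outcome is therefore an ever/never event accumulated over two cycles.

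Under Statistical analysis, the intention-to-treat analysis of this outcome includes all participants, and the missing-data rule is explicit: "Any missing primary outcome data will be supplemented by carrying forward the last recorded data". The one named robustness check is a per-protocol analysis of those who follow the protocol and finish the study. If the two disagree, the results are to be discussed and explained. A complier-average analysis is held in reserve for low compliance.

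Subject withdrawal criteria ends participation for a severe adverse event during chemotherapy, for a schedule change after severe reactions, and for non-compliance ("Subjects do not comply with this study" and its requirements). Sample size expects 20% dropout.

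**The concern.** On this endpoint a patient's status can move in one direction only, from no CRD to CRD. For anyone who leaves before a first episode, the last record is no CRD by construction. Carrying it forward turns an unfinished risk period into a certain prevention success. That is correct only if no such leaver would have had CRD later.

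Event-free leaving is foreseeable: none of the withdrawal reasons requires diarrhea, and the plan expects about 20 of 100 patients to drop out. The reasons concern toxicity and adherence, which may differ between arms. If they do, the rule can create a difference where there is none, or hide a real one, in the analysis that decides the trial. The rule is fixed in the text, so this is a stated method that does not suit the endpoint, and not a detail left for a later document.

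**Working it through.** **Inputs from the article.** Sample size: "the incidence of CRD is 37.5% (6/16) with SXD and 63.4% without SXD, respectively"; two-sided 5% level; 20% dropout; 50 per arm. Statistical analysis: chi-square or Fisher's exact test, with categorical results reported as risk ratios.

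**The plan's own figures.** The dropout step reproduces: 40/(1 − 0.20) = 50. The 40 itself does not (a pooled two-sided calculation gives 58). That is a separate matter, and nothing below depends on it.

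**Inputs the article does not give.** Dropout by arm and its timing. Both are assumed and shown over a range.

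**Formula.** Let p be the true two-cycle CRD risk, d the share of an arm that leaves early, and f the share of the leavers' CRD events that would come after leaving. Only those later events are missed, so

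recorded incidence = p × (1 − d × f).

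The same expression results if d counts only event-free leavers and p × f is their chance of later CRD. It never exceeds p. Rejection rates come from exact binomial enumeration of the uncorrected two-sided chi-square test with 50 per arm. With no loss the test rejects 5.0% of the time under the null.

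**No true effect (p = 63.4% in both arms), more loss on SXD**

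| Loss, SXD vs placebo | f | Recorded, placebo vs SXD | False difference | Two-sided type I error |
|---|---|---|---|---|
| 25% vs 15% | 0.25 | 61.0% vs 59.4% | 1.6 points | 5.5% |
| 25% vs 15% | 0.5 | 58.7% vs 55.5% | 3.2 points | 6.7% |
| 25% vs 15% | 1 | 53.9% vs 47.6% | 6.3 points | 10.7% |
| 30% vs 10% | 0.25 | 61.8% vs 58.6% | 3.2 points | 6.5% |
| 30% vs 10% | 0.5 | 60.2% vs 53.9% | 6.3 points | 10.5% |
| 30% vs 10% | 1 | 57.1% vs 44.4% | 12.7 points | 26.4% |

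Example, third row: 0.634 × (1 − 0.15) = 0.539 and 0.634 × (1 − 0.25) = 0.4755. Swapping the loss between arms gives the same figures in favour of placebo.

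**Planned effect (63.4% vs 37.5%), equal 20% loss**

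- f = 0.5: 63.4% × 0.9 = 57.1% and 37.5% × 0.9 = 33.8%. The difference falls from 25.9 to 23.3 points.
- f = 1: 63.4% × 0.8 = 50.7% and 37.5% × 0.8 = 30.0%. The difference falls to 20.7 points.
- The risk ratio stays at 37.5/63.4 = 0.59 in both cases, because the factor (1 − d × f) cancels.
- Exact power is 76% with 50 per arm and nobody missing, 67% with 40 completers per arm, and under carry-forward 67% (f = 0.5) or 57% (f = 1).

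**The case against.** Several points against the concern stand.

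- A reader might infer that the arm with more dropout always looks better. It does not. A patient who leaves because of severe diarrhea already has the event and is scored correctly. Only loss while still event-free matters.
- A reader might infer that the rule favours SXD. Nothing in the article supports that. It gives a single overall dropout figure, and the placebo is made to resemble SXD in appearance, taste and smell. More event-free loss on placebo would hide a benefit.
- A reader might infer that carry-forward costs a lot of power. Most of the fall from 76% comes from dropout itself: 40 completers per arm give 67%, the same as carry-forward with half of the leavers' events still to come. Only the extreme case, at 57%, is worse.
- With equal loss and equal remaining risk, the risk ratio that the plan reports is unbiased, and the shrunken risk difference errs towards no effect.
- The 26.4% needs a 20-point gap in loss and every leaver's event still to come. The Discussion cites median onsets of about 6 and 11 days under other irinotecan schedules, so many events may fall early in the 42 days, before some leavers go.

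The per-protocol analysis is a partial answer. If leaving is unrelated to CRD risk, completers keep the true rates, and a clash with the main analysis could expose the artefact. But it excludes the leavers and so does not vary the assumption about them. When leaving is related to toxicity or adherence it can be biased too. The complier-average analysis deals with non-compliance, not with missing outcomes.

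**Conclusion.** The concern holds in this form. The missing-data rule is unsuited to a cumulative ever/never endpoint: it can only miss events, and it biases the comparison in favour of whichever arm loses more patients while event-free. The direction is unknown in advance.

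The size rests on assumed loss by arm and assumed timing, with no true effect and 50 per arm. A 10-point gap in loss moves the type I error little when few of the leavers' events are still to come, and roughly doubles it when all are. A 20-point gap does about the same damage when only half are still to come, and much more when all are. If loss and remaining risk are equal across arms, the harm is limited to a smaller risk difference. The documents do not show that a false positive is likely. They do show that the primary result would depend on an untested and implausible assumption about the leavers.

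**What to change.** In Statistical analysis, before unblinding, replace carry-forward for the primary outcome with:

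1. CRD observed before a patient leaves counts as an event.
2. For patients who leave event-free, the two-cycle outcome is multiply imputed by arm, UGT1A1 stratum and length of follow-up.
3. One sensitivity analysis is added: either event-free leavers counted as CRD in both arms, or a tipping-point analysis. This is needed because the imputation also assumes that leavers resemble comparable patients who stayed.

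It would also help to report, by arm, how many patients leave event-free and when, since those two quantities drive the bias. The cost is revised wording, modest programming and possibly a slightly wider confidence interval. No change to recruitment or trial conduct is needed.

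### The per-protocol set used to check the primary result can lose patients because they had the primary event, so agreement or disagreement with ITT need not reflect robustness

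*Protocol article*

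**What the plan says.** Four statements in the protocol article bear on this point.

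- **Outcome** (Primary outcome): CRD is "diarrhea occurring > 24 h after irinotecan administration and up to the completion of both chemotherapy cycles". This is an ever/never outcome.
- **Withdrawal** (Subject withdrawal criteria): participation is terminated if "A severe adverse event (AE) occurs during chemotherapy", or if "The chemotherapy schedule requires modification because of severe adverse reactions to chemotherapy".
- **Analysis sets** (Statistical analysis): ITT covers all participants and is used for the primary outcome. On missing values: "Any missing primary outcome data will be supplemented by carrying forward the last recorded data". The PPS "will only include participants who strictly follow the protocol and finish the study".
- **Role of the PPS** (Statistical analysis): "PPS analysis will be performed to test the robustness of the ITT analysis". The rule for reading the pair is "The results from the two analyses will be considered credible if they are consistent"; if they are not, the article asks for discussion and explanation.

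**The concern.** An ever/never outcome is settled at the first episode. A patient who has severe late diarrhea and is then withdrawn has a complete, positive primary outcome. ITT counts that patient as an event. The PPS, as worded, can exclude the same patient for not finishing, and the reason for not finishing is the event itself. This is selection on the primary outcome, which differs from setting aside patients who did not take their study medication.

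The check also misses a weak spot of the ITT result. A patient who leaves early without diarrhea has an unknown outcome. Carrying the last record forward makes that patient event-free in ITT, and the PPS leaves the patient out. Neither analysis varies what might have happened afterwards.

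At stake is the robustness statement attached to the trial's main result. Disagreement may arise because severe cases were removed, and agreement may be presented as reassurance about missing outcomes that were never examined.

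**Working it through.** **Inputs from the protocol article**
- CRD rates 63.4% without SXD and 37.5% with SXD; 50 per group; two-sided 5% (Sample size).
- Severe diarrhea with irinotecan 11–32% (Background), used here as a range for placebo.

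**Assumptions, not in the article**
- Severe rates under SXD.
- Every severe case is withdrawn and leaves the PPS.
- There are no other losses.

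**Formula.** Let p be the CRD rate in an arm and s the share withdrawn for severe diarrhea, all of whom are CRD cases. Then PPS rate = (p − s)/(1 − s).

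**Starting point.** ITT risk difference = 63.4 − 37.5 = 25.9 points. ITT risk ratio = 0.375/0.634 = 0.591.

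**Worked example, severe 20% placebo and 5% SXD**
- Placebo: (0.634 − 0.20)/0.80 = 0.5425
- SXD: (0.375 − 0.05)/0.95 = 0.3421
- Difference 20.0 points; ratio 0.3421/0.5425 = 0.631

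**All scenarios.** The discordance columns come from 200,000 simulated trials per scenario, 50 per arm, with a pooled z-test on all patients and again after removal of the severe cases. Discordance is the share of trials with ITT P<0.05 in which the reduced set gives P≥0.05. The last column removes the same numbers of patients at random.

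| Severe, placebo/SXD | PPS rates, placebo vs SXD | Risk difference | Risk ratio | Discordance, severe cases removed | Discordance, random loss |
|---|---|---|---|---|---|
| None removed (ITT) | 63.4% vs 37.5% | 25.9 | 0.591 | – | – |
| 11/5% | 58.9% vs 34.2% | 24.7 | 0.581 | 13% | 9% |
| 20/10% | 54.2% vs 30.6% | 23.7 | 0.563 | 22% | 14% |
| 32/15% | 46.2% vs 26.5% | 19.7 | 0.573 | 43% | 21% |
| 20/5% | 54.2% vs 34.2% | 20.0 | 0.631 | 38% | 13% |

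The excess over random loss is about 13 − 9 = 4, 22 − 14 = 8, 43 − 21 = 22 and 38 − 13 = 25 percentage points.

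**Direction**
- Severe 32% in both arms: SXD (0.375 − 0.32)/0.68 = 8.1%, placebo (0.634 − 0.32)/0.68 = 46.2%. The difference widens to 38.1 points and the ratio drops to 0.175.
- No effect on incidence (63.4% in both arms), severe 32% placebo and 8% SXD: placebo 46.2%, SXD (0.634 − 0.08)/0.92 = 60.2%. The ratio is 1.30, an apparent harm. With the severe rates swapped between arms it is 0.77, an apparent benefit.

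The same rule can therefore shrink, enlarge or create a contrast, depending on how severe cases divide between the arms.

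**The case against.** **The rule is not a veto.** A reader might infer that a significant ITT result would be thrown out unless the PPS agrees. The article does not say so. Disagreement leads to discussion and explanation, and ITT on all participants is already the analysis of the primary outcome. This stands and limits the consequence to how robustness is described.

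**Dilution is not the general result.** A reader might infer that the PPS contrast is always too small. On the risk difference it shrinks in the four tabulated scenarios. The article, however, specifies the risk ratio for categorical data, and that ratio is slightly stronger in three of the four. This also stands: no direction can be claimed.

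**Part of the discordance is lost sample size.** Any smaller set near P=0.05 will sometimes lose significance. The random-loss column shows that this accounts for most of the first two figures and about half of the third. Consistency is also not defined in the article as both P values below 0.05. In the simulated trials with a significant ITT result, the PPS estimate kept its direction in more than 99%.

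**The inputs are uncertain.** The 11–32% is a general background figure, the SXD severe rates are assumed, and the article does not define a severe adverse event. The Secondary outcomes section records regimen changes as an outcome, so it is unclear that every patient with severe diarrhea fails to finish. The size is therefore illustrative.

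**Convention and an unseen analysis plan.** ITT with a supportive PPS is ordinary practice, the article adds a CACE analysis if compliance is low, and a finer PPS definition could sit in the analysis plan. But the article itself fixes the completion requirement, the purpose of the PPS and the credibility rule. Read with its own withdrawal criteria, these allow exclusion because of the outcome. A CACE analysis addresses non-adherence and does not repair that.

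**Conclusion.** The point holds in a limited form. As worded, the PPS can exclude patients with an observed CRD event because that event ended their participation. Agreement or disagreement with ITT is then not a sound measure of robustness, and the comparison does not vary the unknown outcomes of patients who left without diarrhea.

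The size ranges from small to material. At severe rates of 11/5% the effect estimates barely move. At 32/15% or 20/5% the risk difference loses about 6 points, and discordance exceeds that from random loss by 22 to 25 percentage points. These figures rest on all severe cases being withdrawn and on assumed severe rates under SXD. The documents do not support saying that the ITT conclusion would be overturned or that the PPS always understates the effect.

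**What to change.** In the Statistical analysis section, for the primary outcome:

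1. Define the PPS by adherence and absence of major deviations up to the first CRD episode or the end of follow-up, whichever comes first. A patient with observed CRD then stays in, whether or not the study is completed.
2. Keep the PPS as a supportive analysis and drop agreement with it as the test of credibility.
3. Base the robustness statement on patients whose outcome is unknown, with a tipping-point table or best/worst-case results by arm.

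This needs no new patients or data and leaves the withdrawal criteria as they are. The cost is a wording change and one more sensitivity table, and the PPS is no longer a pure completer set.
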